### Participants and recruitment

#### RCT among cancer survivors

Cancer survivors of working age (18–63 years at time of diagnosis), with histologically confirmed cancer and a life expectancy of more than 1 year will be recruited. At study entry, eligible cancer survivors have a fixed or temporary employment contract, with at least 6 months left of their contract, and a history of paid work for at least 1 year prior to diagnosis (with ≥8 contracted working hours per week). Cancer survivors can both be at work or (partly) on sick leave when entering the study. Cancer survivors will be recruited 3–18 months post-diagnosis. The cut-off for the maximum time post-diagnosis was set at 18 months for cancer survivors to be able to complete the intervention (with a maximum duration of 6 months) before a potential work disability assessment. According to Dutch legislation, work disability assessments take place after two years of sick leave to determine whether someone is disabled for work or not and may receive work disability benefits or not. Regardless of the outcome of the work disability assessment, employers are allowed to terminate the employment contract after 2 years of sick leave. Moreover, cancer survivors will be eligible for participation in STEPS if they are, or have been, treated with at least radiotherapy and/or chemotherapy. Previous research has shown that cancer survivors who received complex treatments, i.e., chemotherapy, radiotherapy, or a combination thereof, indicated lower work ability than cancer survivors who were treated with surgery alone [22]. Cancer survivors with additional treatment modalities, besides radiotherapy and/or chemotherapy, will be eligible for participation as well.

Cancer survivors will be excluded if their treating physicians consider work unfeasible, if cancer survivors have serious cognitive or psychiatric problems, or other comorbidities that would preclude them from participating in the intervention program, and/or if cancer survivors lack basic proficiency in Dutch. Cancer survivors participating in concurrent studies or rehabilitation programs aimed at sustained employment, or cancer survivors who refuse the involvement of their employer in the STEPS intervention will also be excluded.

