	Contract type (fixed/temporary)	X			A	X	X		A
	Shift work	X			A	X	X		A
	Company size and sector	X			A	X	X		A
	Time since first day of sick leave	X			A				–
	Employment status partner (if applicable)	X			A				–
	(duration of) Caregiving leave				–	X	X		A
Work	Social support from supervisor/colleagues	X			A	X	X		A
	Job insecurity	X			A	X	X		A
	Need for recovery	X			A^c^	X	X		A
	Work accommodation	X			A^c^	X	X		A
	Impact of COVID-19 on work	X			A^c^	X	X		A
	Work attitude	X			A	X	X		A
	Self-efficacy	X			A	X	X		A
	Work-family balance	X			A^c^	X	X		A
	Work intention	X			A	X	X		A
	Fear of COVID-19	X			A	X	X		A
	Expectations regarding return to work	X			A				–
Process measures			X		P				–
Economic evaluation	Quality of life	X	X	X	E				–
	Health care consumption	X	X	X	E				
	Productivity loss	X	X	X	E				

^a^*P* Primary outcome variable, *S* Secondary outcome variable, *A* Additional variable, *M* Modifier, *E* Economic evaluation variables, *P* Process variables

^b^Only completed by participants who were on sick leave at baseline

^c^Only completed by participants who (partly) returned to work

^d^The partner will be asked regarding the medical status of the cancer survivor

**Table 2 Tab2:** List of primary, secondary and additional variables and their assessment methods

		Instrument	# items	Rating scale	Operationalization
Work outcomes	Working hours per week	Asking participants for their current number of actual working hours	1	n/a	Continuous
	Change in working hours (%)	Asking participants for their current number of actual working hours and their contractual working hours at baseline.	1	n/a	Continuous (actual working hours at follow-up as a percentage of contractual working hours at baseline).
	Employment status	Asking participants whether they are at work or not at work	1	n/a	Dichotomous
	Time to return to work	Asking participants about their first day of returning to work, from which we will estimate the number of calendar days between the first day of sick leave and the first day of work, either fulltime or part-time, for at least 28 consecutive days without recurrence.	1	n/a	Continuous
	Sick leave	Asking participants about the number of days they have been on sick leave in the past 6 months	1	n/a	Continuous

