#### RCT among cancer survivors

The primary outcome (i.e., working hours per week) will be assessed by asking cancer survivors about their current number of actual working hours. Hence, the primary outcome ranges from zero hours (for those on full sick leave) up to the number of working hours per week in the participant’s employment contract (for those fully returned to their work). This outcome was chosen as, according to the Dutch system, RTW is typically characterised by a gradual increase in work hours, while this measure is also important for workers trying to retain work. Secondary outcomes measures include: change in working hours (as a percentage of the contract hours at baseline), employment status (at work/not at work), sickness absence days, RRTW, work ability, health-related work functioning (only for cancer survivors who returned to work), time to RTW (only for cancer survivors who were on sick leave at baseline), and health-related quality of life. In addition to abovementioned outcome measures, information on a number of additional parameters (see Table 1 for a full overview) will be gathered, to describe the study sample, to include as potential confounder(s), and/or to conduct subgroup analyses.

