### Economic evaluation RCT

An economic evaluation will be conducted using the societal perspective, alongside the RCT, to assess the cost-effectiveness and cost-utility of the STEPS intervention compared to usual care. The costs will be evaluated with: 1) medical consumption costs (direct health care and direct non-health care costs, e.g. taxi costs obtained from the study declarations), 2) costs related to productivity loss (indirect costs) for both the intervention and the control group, and 3) the costs to deliver the intervention program. The effectiveness will be evaluated with: 1) working hours as measured in the trial (primary outcome), and 2) the utility expressed in quality of adjusted life years (QALYs) [54].

Medical consumption costs will be measured using (a selection of questions from) the iMTA’s medical consumption questionnaire for costs outside the hospital (iMCQ) (e.g., home care, informal help) [55]. Standard costs for the Netherlands [54] and prices of prescribed drugs of the Royal Dutch Society for Pharmacy [56] will be used. Costs related to productivity loss will be measured with (a selection of questions from) the iMTA’s productivity costs questionnaire (iPCQ) [55, 57]. To calculate lost productivity due to sick leave, the net number of days on sick leave will be multiplied by the estimated price of production loss of a worker per day of sick leave, based on age and gender. In case of partial sick leave, it will be assumed that cancer survivors were 100% productive during the hours of partial work resumption. The cumulative net number of days of sick leave will be converted into working hour equivalents based on a Dutch average of 1540 working hours per year, according to the Dutch guidelines [54]. To calculate these costs, the friction cost method will be used, which captures lost productivity costs only until an employee would likely be replaced by someone currently unemployed [58]. Both iMCQ and iPCQ questions will be added to the baseline (T0) and follow-up (T1 and T2) questionnaires.

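### Sick leave is an unweighted day count with no rule for ended contracts, so job loss before T2 can lower the count and partial leave can look like full leave

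*Protocol article*

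**What the plan says.** The Measurements section states that Table 2 sets out how each construct is operationalised, measured and processed for analysis. For sick leave the table gives one item, treated as continuous: "Asking participants about the number of days they have been on sick leave in the past 6 months". Table 1 lists it as a secondary RCT outcome at T0, T1 and T2. Footnotes in Table 1 restrict who completes some other rows, but sick leave has none. The outcome list for the RCT is equally unrestricted: "employment status (at work/not at work), sickness absence days, RRTW, work ability".

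On contracts, Participants and recruitment admits survivors on permanent or temporary contracts "with at least 6 months left of their contract". It also says: "Cancer survivors will be recruited 3–18 months post-diagnosis". It adds that, whatever the disability assessment concludes, "employers are allowed to terminate the employment contract after 2 years of sick leave". Under Randomization, everyone allocated to an arm is followed.

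On partial leave, survivors who are partly sick-listed are eligible, and the primary outcome is justified by the fact that "RTW is typically characterised by a gradual increase in work hours". The economic evaluation uses net days: "the net number of days on sick leave will be multiplied by the estimated price of production loss", and hours of partial resumption count as fully productive. That rule is stated for productivity costs only. Selected iPCQ questions are asked at T0, T1 and T2.

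In the RCT columns of Table 1, contract type and time since the first day of sick leave are collected at T0 only. Employment status at follow-up has two values, at work or not at work.

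**The concern.** A count of days on sick leave presupposes a job to be on leave from. Once the contract has ended, a participant may reasonably answer that there were few or no such days. A low count is the good end of the scale, so a failure of work retention can be scored as an improvement in sick leave.

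The count also ignores how much of each day is worked. The programme aims at a gradual rise in hours, yet a participant moving from no work to three-quarters of contract hours may show no change on this outcome.

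At stake is the reading of a between-arm difference in sick days at T2, which the analysis section reports separately from T1. If the arms differ in contract loss, part of that difference can point the wrong way. Contract status is not asked at follow-up, so the analyst could not tell how much.

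**Working it through.** **The plan's own figures.** None is given for sick leave. The only RCT sample size is for weekly hours: n per group = 2 × (1.960 + 0.842)² × 13² / 5.5² = 87.7, rounded up to 88. For attrition, 176 / 0.75 = 234.7, against 236 planned. Both agree with the protocol, and neither depends on the point made here.

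**Inputs.** Entry at m months after diagnosis, m from 3 to 18; T1 at study month 6 and T2 at month 12; at least 6 months of contract left at entry; termination allowed after 24 months of leave. The recall window is 6 months, taken as 182 days. At T2 it covers study months 6 to 12, that is, months m + 6 to m + 12 after diagnosis. T2 itself falls at 15 to 30 months.

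**Route 1: a contract that runs out.** Take a participant on full leave until the contract ends at study month s (6 to 12), who counts no days after that. Days reported at T2 = 182 × (s − 6) / 6.

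| Contract ends at study month | Days reported at T2 |
|---|---|
| 6 | 0 |
| 7 | 30 |
| 8 | 61 |
| 9 | 91 |
| 10 | 121 |
| 11 | 152 |
| 12 | 182 |

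**Route 2: two years of leave.** Assume unbroken leave from diagnosis and termination as soon as it is allowed. The 24-month point falls at study month 24 − m, so days reported at T2 = 182 × (18 − m) / 6 for m from 12 to 18.

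| Entry, months after diagnosis | Days reported at T2 |
|---|---|
| 12 or earlier | 182 |
| 15 | 91 |
| 18 | 0 |

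**T1.** Its window ends at month m + 6 after diagnosis, at most 24, and the contract had at least 6 months to run at entry. Neither route therefore bites before T1. Earlier dismissal or resignation could still do so.

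**Effect on the comparison.** Shift in the mean difference = (difference between arms in the proportion losing the contract) × (days understated per person). The documents give neither term. For an assumed difference of 5 percentage points:
- every contract ends by study month 6 and each person reports 0 instead of 182: 0.05 × 182 = 9.1 days;
- contracts end at study month 9: 0.05 × 91 = 4.6 days;
- equal loss and equal timing in both arms: 0 days.

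The shift favours the arm that loses more contracts.

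**Partial leave.** If every day of partial leave is counted as a day, the gross count over the window is 182. Net days = 182 × (1 − share of contract hours worked).

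| Share of hours worked | Gross days | Net days |
|---|---|---|
| 0% | 182 | 182 |
| 25% | 182 | 136.5 |
| 50% | 182 | 91 |
| 75% | 182 | 45.5 |

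**The case against.** The strongest reply is that Table 2 is a one-line summary in a journal article. The questionnaire may tell respondents how to count partial days and what to answer without a contract, and some participants who lost their job may still report sick days. This stands, and it is why the claim is that the count can be too low, not that it will be. It does not remove the point. The article presents Table 2 as the measurement and scoring of each construct, and an analysis plan cannot recover contract status that follow-up never asked for.

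Second, other outcomes register job loss. Actual weekly hours, hours as a percentage of baseline contract hours, and employment status all score job loss without re-employment at the bad end. The primary outcome was chosen precisely because return is gradual. This stands too. A reader might infer that the trial overlooks job loss, or that any difference in sick days is uninterpretable; the documents support neither. What these outcomes do not do is separate job loss from full leave with a running contract: both give 0 hours and not at work.

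Third, the exact zero needs a contract end close to study month 6 or, on the two-year route, entry at the 18-month limit, unbroken leave from diagnosis and immediate termination. Employers are permitted to terminate, not obliged to. This is correct: a later end gives an understated count, not zero.

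Fourth, those at risk can be partly identified at baseline from contract type and time since the first sick day. That would support a sensitivity analysis by risk group, but it does not show whose contract actually ended.

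Finally, counting all days after contract end as sick days would replace sick leave with another construct. That is fair, and the proposal below confines it to a sensitivity analysis.

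**Conclusion.** The point holds for a secondary outcome, mainly at T2. As defined, the count can fall when a participant loses the job, and it can fail to move as hours are resumed. The protocol's own entry and follow-up rules make both situations foreseeable.

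The size cannot be determined from the documents. The 9 days per 5-point difference in contract loss is a ceiling: it assumes that every affected contract ends by T1 and that each such participant answers 0 instead of 182. The 5 points are an illustration, not an estimate. The partial-leave figures assume that each partial day is reported as a whole day.

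A reader might infer that the trial's main result is biased. It is not: the primary outcome, its analysis and the sample size are unaffected. This is an inexpensive improvement worth making, not a flaw that invalidates the design.

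**What to change.** 1. Ask at T1 and T2 whether the baseline contract is still running and, if not, when and why it ended. Report contract retention by arm beside sick leave.
2. Analyse sick leave as net days, applying the partial-resumption rule of the economic evaluation and the iPCQ questions already planned at all three time points. Because only a selection of those questions is used, confirm that it captures hours of partial work over the full 6 months.
3. Do not score days after contract end as zero sick leave. Report sick days together with contract status, and add a sensitivity analysis that counts days after a health-related contract end as not worked.

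The cost is one extra follow-up item (with a short follow-on on date and reason), slightly more respondent burden and a revised scoring rule. Recruitment and the primary analysis do not change.

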	Readiness for return to work	The translated and adapted Dutch version [25] of the original RRTW questionnaire [15]. There are a number of items for each of the phases, with each item being scored on a 1 to 5 scale. Each RRTW stage will be scored by averaging all items within that stage. The stage with the highest summary score was considered the stage the participant was in. In case of a tie between stages, the lowest RRTW stage will be adopted. Based on this participants will be classified in any of the six RRTW phases.	21	6 stages	Ordinal
	Work ability	Single question of the Work Ability Index (WAI) [27], asking participants to estimate their current work ability compared with their lifetime best on 0 to 10 scale (0 = cannot work at all; 10 = best ever);	1	10-point scale	Continuous
Health outcomes	Health-related work functioning	The validated [28] 27-item Work Role Functioning Questionnaire (WRFQ) [29], distinguishing five different work domains: work scheduling demands, mental demands, social demands, physical demands, and output demands (range 0 to 100). Higher scores indicate better work functioning.	27	0 to 100	Continuous
	Health-related quality of life	For patients: the European Organization for Research and Treatment of Cancer Quality of Life Questionnaire – Core 30 (EORTC QLQ C-30) [30]). This 30-item list consists of five multi-item functional scales (i.e., physical, role, emotional, cognitive, and social), three multi-item symptom scales (i.e., fatigue, pain, and nausea and vomiting), six single-item (i.e., dyspnoea, insomnia, appetite loss, constipation, diarrhoea, and financial impact), and a two-item global health and quality of life scale, all with a scoring range from 0 to 100. A higher score on the functional and global health and quality of life scales indicates better quality of life, while on the symptom scales, a higher score indicates a higher level of symptom burden. A summary score will be generated, calculated as the mean of all combined scale scores, excluding financial impact and the global health and quality of life scale.	30	0 to 100	Continuous
		For partners: 12-item short-form health survey (SF-12) [31], expressed in t-score.	12	n/a	Continuous
	Caregiver burden	The ‘Ervaren Druk door Informele Zorg-plus’ (EDIZ) [32], consisting of 15 items, ranging from 0 to 1, higher scores indicate a higher caregiver burden	15	0 to 15	Continuous

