### Statistical analyses

For hardcopy questionnaires, data entry will be verified by a 10% double data entry check. In preliminary analyses, for both the RCT and cohort study, item frequencies and missing data will be examined. Patterns of missing data will be assessed to determine non-ignorable dropout. Scores for the included scales will be calculated according to established scoring algorithms (as described in more details in Table 2). All analyses will be performed using SPSS 22.0 [45], and a two-tailed significance level of 0.05 will be considered statistically significant.

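### Table 2 defines the QLQ-C30 summary score as a mean of scales that run in opposite directions and states neither a reversal nor a direction; applied literally, the score is compressed and can change sign

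*Protocol article*

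**What the plan says.** The rule is in the Protocol article, Methods, Measurements, Table 2, in the row for the survivors' health-related quality of life. That cell does four things.

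- It lists the components. There are five functional scales, three symptom scales built from several items each, and a separate group of "six single-item (i.e., dyspnoea, insomnia, appetite loss, constipation, diarrhoea, and financial impact"). The global scale comes last. Every component is scored from 0 to 100.
- It gives the direction of the functional and global scales: "A higher score on the functional and global health and quality of life scales indicates better quality of life".
- It gives the opposite direction for the others: "on the symptom scales, a higher score indicates a higher level of symptom burden".
- It defines the summary score as "calculated as the mean of all combined scale scores, excluding financial impact and the global health and quality of life scale".

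Nothing in the cell, or elsewhere in the article, mentions reversing the symptom scales before averaging, and the direction of the resulting summary is not given. The Statistical analyses section has a general scoring rule: "Scores for the included scales will be calculated according to established scoring algorithms (as described in more details in Table 2"). The Measurements text likewise presents Table 2 as the place that shows how constructs are processed for analysis.

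Health-related quality of life is a secondary outcome of the RCT (Table 1, and the RCT part of Measurements). It is to be analysed by GEE, with the effect reported as a beta and 95% confidence interval.

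**The concern.** A mean of scales that point in opposite directions is not a quality-of-life score. Gains in function raise it, relief of symptoms lowers it, and the two partly cancel. Because more symptom components than functional ones enter the mean, the symptom side can dominate and turn the sign.

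The cell is specific enough to be followed: it names the operation and both exclusions. It leaves out the one step that makes the operation valid. The general rule on scoring does not clearly supply that step, because it cites Table 2 for the details.

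At stake is the reading of one secondary treatment effect. If the literal rule were programmed, a benefit spread over function and symptoms could be reported as a small deterioration. Even with correct programming, the sign of the reported beta cannot be interpreted from the article, because the direction of the score is not stated. Other Table 2 rows do state it, for example those for work functioning, caregiver burden and fatigue. The Randomization section says that those who analyse the results are not blinded, which is a further reason to have the scoring rule complete in writing beforehand.

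**Working it through.** The plan gives no figure for this score, so there is none to reproduce. The check applies the Table 2 definition directly.

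**Inputs**

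- Functional scales: 5, higher = better (Table 2).
- Multi-item symptom scales: 3, higher = worse (Table 2).
- Single items: 6 listed, less financial impact, leaves 5. Their direction is not stated separately. *Assumption:* higher = worse, like the symptom scales.
- The global scale is excluded.
- Components in the mean: 5 + 3 + 5 = 13, of which 5 are functional and 8 are symptom scales or items. Each runs from 0 to 100.

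**Formulas**, with F the mean functional score and S the mean symptom score:

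- Literal: (5F + 8S)/13
- With reversal: (5F + 8(100 − S))/13

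**Extremes**

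| State | Literal | With reversal |
|---|---|---|
| Best health (F = 100, S = 0) | 500/13 = 38.5 | 1300/13 = 100 |
| Worst health (F = 0, S = 100) | 800/13 = 61.5 | 0/13 = 0 |

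The distance from best to worst health is 61.5 − 38.5 = 23.1 points (300/13) instead of 100, and it runs the wrong way. This is a span between two health states. It is not the full range of the literal score, which can still reach 0 (all 13 components at 0) and 100 (all at 100).

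**Changes.** Let a be the mean functional gain and b the mean symptom improvement, in points. The literal change is (5a − 8b)/13 and the change with reversal is (5a + 8b)/13.

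| Change | Literal | With reversal |
|---|---|---|
| a = b = 5 | −15/13 = −1.2 | +5 |
| a = b = 10 | −30/13 = −2.3 | +10 |
| a = b = 20 | −60/13 = −4.6 | +20 |
| Function only, a = 10 | +50/13 = +3.8 | +50/13 = +3.8 |
| Symptoms only, b = 10 | −80/13 = −6.2 | +80/13 = +6.2 |

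**Condition for a wrong sign.** When neither domain worsens and symptoms improve, the literal change is negative if 5a < 8b, that is, if a < 1.6b.

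**Sensitivity to the assumption.** If the five single items instead ran higher = better, the literal score would be (500 + 500)/13 = 76.9 at best health and 300/13 = 23.1 at worst. The score would be compressed to a span of 53.8 points but not inverted, and a uniform 10-point improvement would give (50 + 50 − 30)/13 = +5.4.

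**The case against.** The strongest defence is that silence is not a decision. The cell does not say that symptom scales stay unreversed. The Statistical analyses section commits the trial to established algorithms, and Table 2 is visibly not a complete scoring manual: the SF-12 row, for instance, says little more than that a t-score is used. The opposite directions are described just before the summary is defined, so the authors knew of them. A journal article may condense such steps and leave the syntax to a fuller document that is not shown here.

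Most of this stands as a limit on the consequence. A reader might infer that the trial will compute a wrong score, or that better health always lowers it. The documents support neither. Correct scoring is plausible under the general rule, and on the literal formula a gain in function alone moves the score the right way. The inversion also depends on an unstated direction for the single items.

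It does not dispose of the point. The article does more than leave scoring to another document: it states a formula, names both exclusions and omits the step on which validity depends. The general rule then refers back to that same table. Followed as written, the rule gives an invalid score whichever way the single items run, since it is compressed in both cases.

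**Conclusion.** The point holds as a defect in the stated rule. Table 2 averages oppositely directed scales with no stated reversal and no stated direction for the result. Taken literally, with single items scored higher = worse, it gives 38.5 for best health and 61.5 for worst, and −2.3 instead of +10 for a uniform 10-point improvement. The sign is wrong when both domains improve and the mean functional gain is less than 1.6 times the mean symptom gain.

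A miscomputed outcome is a risk of the wording and not an established consequence. The reach is also limited. This is one of the eight secondary RCT outcomes listed. The primary outcome (working hours), the sample size based on it, and the QALYs (taken from the EQ-5D-5L) are unaffected.

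**What to change.** Replace the summary-score sentence in Table 2 with: *mean of the 13 scale scores after reversing each symptom scale and symptom item (100 − score), excluding financial impact and global health/QoL; higher = better.* Under this rule best health scores 100, worst scores 0, and a uniform 10-point improvement gives +10.

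The cost is one sentence in the table and, if the scoring syntax lacks the reversal, one line there. No new data are needed. The wording should be settled before the outcome is scored.
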